## Methods/design

### Study design

This will be a randomized controlled trial. To meet ethical requirements and considering the particularity of ASD, this study will not employ a blind design. The trial will be conducted at Hunan University of Chinese Medicine, China, from November 2020 to December 2022. Eligible children will be randomly divided into the pediatric Tuina plus conventional treatment group or the conventional treatment group based on a computer-generated random table at a ratio of 1:1. Efficacy will be assessed using the Childhood Autism Rating Scale (CARS) and the Autism Treatment Evaluation Checklist (ATEC). Before study commencement, all participants will be assessed using a scale by a third party not involved in the study. The baseline level of the participants will be determined at the time of enrollment; further, the participants will be evaluated again after the 30th treatment, with a follow-up period of 6 months postoperatively. Figure 1 shows the flowchart of the study.

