#### Elimination criteria

1. Children who do not complete 30 intervention sessions following the research protocol

2. Children who received other interventions that may affect the study results

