#### Drop-out criteria

1. Children experiencing adverse events during the trial, such as pneumonia and skin disease, and who could not adhere to the Tuina therapy.

2. Children whose guardian perceived the treatment as ineffective and therefore terminated the treatment.

3. Children withdrawing from the treatment at the original rehabilitation institution or after being transferred to a different rehabilitation institution.

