#### Primary outcomes

The main efficacy score will be based on the CARS, which covers interpersonal relationships, imitation, and other 15 aspects, with a total score of 60 points. Each aspect will be scored using a four-point scale: age-appropriate (score 0), mildly abnormal (score 1), moderately abnormal (score 2), and severely abnormal (score 3). Participants with a score < 30, 30–35, and ≥ 36 are considered as non-autistic, moderately autistic, and severely autistic, respectively. Outcomes will be evaluated after the 30th treatment session. Follow-up efficacy assessment will be performed at 6 months post-treatment. The difference in CARS before and after the intervention will be considered significant, effective, and ineffective if the reduction is greater than 10, 5–10 (inclusive), or less than 5 points, respectively [29]..

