### Sample size estimation

The sample size calculation for this study should use a superiority test with two independent sample means to test the scientific hypothesis that both Tuina and conventional treatment are effective for treating children with ASD, but the efficacy of the Tuina treatment may be superior. According to the primary outcome, a difference of more than 5 in the CARS from before to after the intervention is considered to indicate effectiveness [29]. In our initial clinical study [31], the mean value of the difference in CARS from before to after the intervention was 7.5 in the Tuina group (*n* = 22) and 4.27 in the control group (*n* = 22), with a combined standard deviation of 4.43. The test of superiority was a one-sided test, with the test level set at *α* = 0.025 and *β* = 0.2, power=0.8 The ratio of sample size between the two groups was set at a ratio of 1:1, and the shedding rate was 10%. The above data were entered into the interface of “Sample Size Calculation” of the Meisi Medical APP (Shanghai Meisi Medical Technology Co.). Based on the results, 108 cases in each group were deemed necessary. This research is funded by the Hunan Provincial Department of Science and Technology and other institutions that seek to benefit children with ASD. Therefore, we plan to include 200 cases in each group, for a total of 400 cases.

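### Stopping because the guardian sees no effect is a drop-out criterion, and a Tuina child who stops early then has no planned CARS assessment, so missing data depend on the perceived outcome

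*Protocol article*

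**What the plan says.** Four parts of the protocol article bear on this.

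- **Drop-out criteria, item 2:** "Children whose guardian perceived the treatment as ineffective and therefore terminated the treatment". Item 3 separately covers children who leave or change their rehabilitation institution.
- **Elimination criteria, item 1:** "Children who do not complete 30 intervention sessions following the research protocol".
- **Primary outcomes:** "Outcomes will be evaluated after the 30th treatment session", and "Follow-up efficacy assessment will be performed at 6 months post-treatment". The change in CARS "will be considered significant, effective, and ineffective if the reduction is greater than 10, 5–10 (inclusive), or less than 5 points, respectively".
- **Sample size estimation:** the calculation assumes that "the shedding rate was 10" per cent, with no split by arm or by reason.

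Under Study design, "this study will not employ a blind design". The Allocation section keeps assessors and analysts unaware of the groups and says that only the Tuina physician knows them. But the Tuina group section has a parent or relative holding the child during each session, so families know which arm they are in. Statistical analyses names a t-test or a rank-sum test, two-sided at 5%.

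**The concern.** The trigger in item 2 is the perceived result of treatment. The primary outcome has a category for children who do not improve enough, and the children most likely to belong there are among those the rule classes as drop-outs. If they are not scored, the mean improvement and the response rate in their arm are computed on a group selected for doing better.

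A two-sample test on the scored children cannot undo that selection, and neither can a larger sample: enrolling more children to cover shedding restores precision but does not remove bias. An analysis set defined later cannot supply scores that were never collected. The selection is also avoidable, because the rating is done by a third party and does not require the child to be on treatment.

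**Working it through.** **Reading the rules together.** Take a Tuina child whose guardian ends treatment at, say, session 15 because nothing seems to change. The child is a drop-out under item 2. The child has fewer than 30 sessions, so the elimination rule also applies. The primary assessment follows the 30th session, which this child never reaches. No other section gives an assessment date for such a child. For control children the chain is less clear, because the article does not say what the 30th session means for a child receiving no Tuina.

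**Inputs (Sample size estimation).** Mean CARS reduction 7.5 (Tuina) and 4.27 (control), difference 3.23, SD 4.43, shedding 10%, 200 per arm.

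**The plan's own figure.** A standard superiority calculation gives 2 × (4.43 × (1.960 + 0.842) / 3.23)² = 29.5, so 30 per group, and 30/0.9 = 34 after 10% loss. It does not reproduce the stated 108. That is a separate matter: the illustration below uses only the means, the SD, the 10% and the 200 per arm.

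**Illustration.** Assumptions, not in the document: CARS change is normal, there is no true effect (both means 4.27), and those lost are a random subset of children improving by less than 5.

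1. z = (5 − 4.27)/4.43 = 0.165, so P(reduction < 5) = 0.565. True response rate = 0.435.
2. Mean of those below 5 = 4.27 − 4.43 × 0.3936/0.5654 = 1.19.
3. Lose 10% of the Tuina arm, all from that group: remaining mean = (4.27 − 0.10 × 1.19)/0.90 = 4.61. Spurious advantage = 4.61 − 4.27 = 0.34.
4. SE = 4.43 × √(1/180 + 1/200) = 0.455, and 0.343/0.455 = 0.753.
5. Two-sided rejection = P(Z > 1.960 − 0.753) + P(Z < −1.960 − 0.753) = 0.114 + 0.003 = 11.7%.
6. Observed response rate = 0.4346/0.90 = 48%, against a true 43%.

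**Other loss patterns, same model, no true effect**

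| Loss among children improving < 5 | Spurious difference | Two-sided error |
|---|---|---|
| 10% of Tuina, 0% of control | 0.34 | 11.7% |
| 5% of Tuina, 0% of control | 0.16 | 6.5% |
| 7% of Tuina, 3% of control | 0.14 | 6.0% |
| 5% of each arm | 0 | 5.0% |

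**Equal tendency to leave, with the pilot effect true.** P(reduction < 5) is 0.286 in Tuina (mean of those children 2.24) and 0.565 in control (mean 1.19). Let 20% of these children leave each arm.

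- Tuina: loss 0.2 × 0.286 = 0.057. Remaining mean = (7.5 − 0.057 × 2.24)/0.943 = 7.82.
- Control: loss 0.2 × 0.565 = 0.113. Remaining mean = (4.27 − 0.113 × 1.19)/0.887 = 4.66.
- Observed difference = 7.82 − 4.66 = 3.16, slightly below the true 3.23.

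**The case against.** **Exclusion is inferred.** A reader might infer that the article orders drop-outs to be left out of the analysis. It does not say so. It names tests but no analysis set, and an unseen statistical analysis plan may well define one by randomisation. That stands. What remains is about conduct: the stated rules give an early stopper no assessment date, and no analysis set can recover a score that was not taken.

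**Bias towards Tuina.** A reader might also infer that the rule favours Tuina, since Tuina is the added element a guardian can end while the child stays at the institution. The document does not establish this. Item 2 speaks of the treatment in general, item 3 makes a child who leaves the institution a drop-out too, and on the pilot figures more control children fall below 5 points (56.5% against 28.6%). Loss could run either way.

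**The 10% case is severe.** It assigns an all-cause allowance to one reason, one arm and only poor responders. That is correct; the smaller cases in the table are at least as plausible. A still harsher case, in which guardians remove exactly the worst-scoring children, would require them to predict the third party's CARS ranking, and nothing in the document supports that.

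**Perceived failure is not a CARS reduction below 5.** True, and it is a reason to measure these children rather than assign them a result.

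**The 30-session rule already catches them.** Largely true for Tuina children, so changing item 2 alone would achieve little. The repair has to cover both rules and the timing of the assessment.

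**Conclusion.** The concern holds as a fault in the stated conduct rules. A Tuina child who stops early because the guardian sees no effect is classed as lost and has no planned CARS assessment, so missingness depends on the perceived outcome in a trial open to guardians. The possible bias ranges from none, or a slight shift against Tuina (3.16 instead of 3.23), to about 0.34 points in favour of Tuina with a two-sided error near 12%. The upper figure rests on normal CARS changes, no true effect, and the whole 10% loss falling among poor responders in the Tuina arm. The actual share and its split by arm are unknown, so neither a direction nor a firm size can be claimed.

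**What to change.** - Make drop-out item 2, and the 30-session rule as it applies to these children, a reason for stopping treatment and not for leaving the trial. The guardian's freedom to stop is unchanged.
- Record the date and reason for stopping.
- Have the third party rate CARS and ATEC at the calendar time of the end-of-treatment assessment and at 6 months, unless the guardian withdraws consent to assessment. On the schedule in the Tuina group section (five sessions a week, 30/5 = 6 weeks) the first date is about week 6. The caption of Fig. 1 gives two sessions a week for 6 weeks, which is 12 sessions, so the two passages must be reconciled before the date is fixed.
- Analyse these children in their randomised group.
- Counting stoppers without a score as ineffective should be at most a sensitivity analysis of the response categories. It imputes an unobserved result and does not bear on the planned comparison of means.

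The cost is protocol wording and some effort to bring families back for assessments already in the schedule. The observed effect may be smaller. Trial status reports that recruitment had ended and the intervention phase was starting, so continued assessment was still feasible at that point.

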### Interventions

#### Control group

Based on the training of the autism organization mentioned above in this protocol, the control group will strictly follow the five schedule sessions of applied behavior analysis training, five key skill training sessions, five music group training sessions, five oral muscle training sessions, and five sensory training sessions per week. Only teachers with a background in special education will participate in the study.

#### Tuina group

The Tuina group will receive a total of 30 sessions of pediatric Tuina (five sessions per week for 6 weeks, and a follow-up session at the 12th week after the end of treatment). From the perspective of humanistic care, to make the child feel safe, the child will be held by the parents or relatives during the session and placed in a sitting position. Tuina will be performed face to face. When performing acupoint Tuina on the back, the child will lie on his parents or relatives in a prone position.

To standardize the Tuina manipulation, only certified Chinese medicine physicians with 3 months of training in Tuina techniques will perform the procedures. The acupoint prescriptions are mainly based on the TCM theory of the relationship between *Du Meridian* and the *Brain*. After gathering clinical evidence and soliciting the opinions of experienced Tuina experts, we have summarized the following acupoints and manipulation times of Tuina. Table 1 presents the detailed information.

**Table 1 Tab1:** Tuina acupoints, manipulation times, and methods

Acuponits	Location	Methods	Times
Tianmen	Located from the middle of the eyebrows to the front hairline in a straight line	Linear-pushing with the finger	24
Kangong	Located on a horizontal line connecting both brows	Wiping with the finger	24
Taiyang (temple)	Flat part at each side of the forehead	Pressing-kneading with the finger	24
Wangu (GB12)	Located in the posterior inferior depression of the mastoid behind the ear and above the attachment of the sternocleidomastoid muscle		24
Yamen (GV15)	Located on the nape, 0.5 Cun above the middle of the posterior hairline, and below the first cervical vertebra.		100
Fengfu (GV16)	Located on the nape, when the posterior hairline is straight up 1 Cun, the extraoccipital protuberance is straight down, and the depression between the trapezius muscles		100
Baihui (GV20)	Located on the head, 5 Cun above the middle of the front hairline.		100
Shuigou (GV26)	Located on the face, at the intersection of the upper 1/3 and middle 1/3 of the sulcus		100
Du Meridian	Located on the midline of the back. Tuina therapy is mainly performed from the thoracic spine to the sacral spine.	Pressing-kneading with the finger	20
		Pinching with the finger	20
		Pushing with the finger	300
Jianjing (GB21)	Located under the spinous process of the seventh cervical vertebra, on the midpoint of the line with the acromion	Grasping with the finger	10

### Outcome assessment

The results will be evaluated by a third party otherwise uninvolved in the study. This study will be conducted at the Mental Health Center of the Second Xiangya Hospital of Central South University, Hunan Province, China.

#### Primary outcomes

The main efficacy score will be based on the CARS, which covers interpersonal relationships, imitation, and other 15 aspects, with a total score of 60 points. Each aspect will be scored using a four-point scale: age-appropriate (score 0), mildly abnormal (score 1), moderately abnormal (score 2), and severely abnormal (score 3). Participants with a score < 30, 30–35, and ≥ 36 are considered as non-autistic, moderately autistic, and severely autistic, respectively. Outcomes will be evaluated after the 30th treatment session. Follow-up efficacy assessment will be performed at 6 months post-treatment. The difference in CARS before and after the intervention will be considered significant, effective, and ineffective if the reduction is greater than 10, 5–10 (inclusive), or less than 5 points, respectively [29]..

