### Eligibility criteria

#### Inclusion criteria

1. Diagnosis made by a psychiatrist based on the diagnostic criteria for ASD of the Diagnostic and Statistical Manual of Mental Disorders (DSM-5)

2. Age: 2–6 years old

3. CARS score ≥ 30 points

4. The guardian of the child is informed of the study and the child is compliant with the treatment cycles

5. No history of participation in other observational studies or unplanned interventions within the past 30 days, such as acupuncture and herbal treatment that may affect the study results

6. No history of other serious diseases that may affect the outcomes, including organic pathologies, coagulation disorders, congenital heart disease, and epilepsy

7. No history of chronic or acute infections, such as pneumonia

8. No history of other psychiatric disorders, such as ADHD

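### The CARS item coding (0 to 3) cannot produce the stated total of 60, so the entry cut-off of 30 and the severity bands have no settled meaning

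*Protocol article*

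**What the plan says.** The Primary outcomes section of the protocol article makes four statements about the CARS:

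- Content: it "covers interpersonal relationships, imitation, and other 15 aspects".
- Total and item coding: it is a scale "with a total score of 60 points. Each aspect will be scored using a four-point scale: age-appropriate (score 0), mildly abnormal (score 1"), then "moderately abnormal (score 2), and severely abnormal (score 3").
- Bands: "Participants with a score < 30, 30–35, and ≥ 36 are considered as non-autistic, moderately autistic, and severely autistic, respectively".

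The same total decides entry, since the Inclusion criteria require "CARS score ≥ 30 points". Response is judged on change from before to after the intervention, by whether "if the reduction is greater than 10, 5–10 (inclusive), or less than 5 points, respectively". No other section gives a different item coding or reconciles the coding with the total.

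**The concern.** The highest item score is 3, so a total of 60 would need 20 items, and no section mentions 20. One of the two statements is therefore wrong, and the article does not show which.

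The trial uses the absolute total twice: to admit children and to class their severity. Both uses depend on what a score of 30 or 36 means, and that depends on the item coding. If the lowest item score is 0, a total of 30 describes a much more affected child than if the lowest is 1. At stake are who was eligible, how baseline severity is described, and to which children the result applies.

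**Working it through.** **Inputs** (Primary outcomes, except the entry cut-off, which is in the Inclusion criteria)

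- Items: 15 on the sensible reading; 2 + 15 = 17 on the literal one
- Printed item scores: 0, 1, 2, 3
- Stated total: 60
- Entry cut-off: 30; bands: below 30, 30 to 35, 36 or more

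**Step 1. Try to reproduce the stated total.** Maximum total = number of items × highest item score.

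| Items | Coding | Range | Maximum is 60? |
|---|---|---|---|
| 15 | 0 to 3 (as printed) | 0 to 45 | no |
| 17 | 0 to 3 (literal item count) | 0 to 51 | no |
| 15 | 1 to 4 | 15 to 60 | yes |
| 17 | 1 to 4 | 17 to 68 | no |

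The stated 60 is not reproduced by the printed coding under either item count. Of these variants, only 15 items scored 1 to 4 gives it.

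**Step 2. Offset between the two candidate codings, with 15 items.** Each item differs by 1, so the total differs by 15 × 1 = 15 for identical ratings.

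**Step 3. Effect on the cut-offs.**

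- A total of 30 or 36 under 1 to 4 coding is 30 − 15 = 15 or 36 − 15 = 21 under 0 to 3.
- A total of 30 or 36 under 0 to 3 coding is 30 + 15 = 45 or 36 + 15 = 51 under 1 to 4.
- The cut-off of 30 lies 30/45 = 66.7% of the way up the 0 to 45 range, but (30 − 15)/45 = 33.3% of the way up the 15 to 60 range. For 36 the figures are 36/45 = 80.0% and (36 − 15)/45 = 46.7%.

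**Step 4. The same child under each coding.**

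| Rating on all 15 items | 0 to 3 | 1 to 4 |
|---|---|---|
| Mildly abnormal | 15 × 1 = 15: not eligible, non-autistic band | 15 × 2 = 30: eligible, moderate band |
| Moderately abnormal | 15 × 2 = 30: just eligible, moderate band | 15 × 3 = 45: eligible, severe band |

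Every child scoring 30 to 44 under 1 to 4 coding scores 15 to 29 under 0 to 3 coding and fails entry.

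**Step 5. Effect on change.** With one coding throughout, (pre + 15) − (post + 15) = pre − post. The offset cancels. The response categories at 5 and 10 points, the comparison of change between groups, and the inputs in Sample size estimation (mean changes 7.5 and 4.27, combined SD 4.43) are the same under either coding.

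**The case against.** The strongest reply is that this is a slip in describing the scale. If the form in use is scored 1 to 4, the data are sound and only the article is wrong. Efficacy is judged on change, where a constant offset disappears. A third party does the assessments and a third-party institution determines eligibility, which makes inconsistent coding less likely. All of this stands, and it confines the point to absolute scores. It does not remove the point, because the erroneous text is the scoring rule behind an entry criterion and the article does not say which coding was applied.

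A reader might infer that the treatment effect itself is at risk, since a 15-point artefact would exceed the 10-point response threshold and equal 15/4.43 = 3.4 planning SDs. The documents do not support this. It would need the coding to switch between visits within the same child, and nothing in the article suggests that. Different codings between assessors would still cancel for any child coded the same way at both visits. The ratio also sets an offset in score level against an SD of change.

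A reader might also infer that 1 to 4 coding is proven. It is the coding that fits 15 items and a total of 60, but that takes the 60 as correct. Changing the total to 45 would also remove the arithmetic conflict, since 30 and 36 both lie within 0 to 45. The form actually used must settle it.

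**Conclusion.** The contradiction is certain: with items scored 0 to 3 the maximum is 45 or 51, never 60. Its size, 15 points on every child's absolute score, rests on two assumptions: that the scale has 15 items, and that the alternative coding is 1 to 4. With 17 items the offset would be 17.

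The consequence is limited to eligibility, severity class and baseline description. If one coding was used throughout, there is no consequence for the change-score comparison, the response categories or the planning inputs. If the forms were scored 1 to 4, the defect is confined to the article's text. If they were scored 0 to 3 with the cut-off of 30, the trial admitted only children who would score 45 or more under 1 to 4 coding, a markedly more severe population. The scoring paragraph needs correcting because an entry criterion depends on it.

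**What to change.** 1. In Primary outcomes, state one item count, one item coding, and a total and cut-offs that agree with them, taken from the CARS form actually used. Fifteen items scored 1 to 4 is the four-point coding that gives 60. If the form shows otherwise, the total must change and the entry cut-off and bands must be reconciled with it.
2. Check once that all completed baseline forms used that coding. These forms should exist: Trial status says recruitment ended in September 2021, and Allocation places the baseline assessment before randomization.
3. If any forms used the other coding, convert them to the common scale (a shift of 15 points with 15 items) before applying the cut-offs or computing change.
4. Report any effect on who was screened in or out. Recoding cannot restore children already excluded, so this would have to be described as a limit on the population studied.

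The cost is one corrected paragraph and one check of existing forms if the coding proves consistent with the cut-offs. If it does not, add the recoding and a statement on screening. The loss of any wrongly excluded children cannot be repaired.
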